**Objective 4**			
	Question 8		Are there undesirable side effects of the full-component intervention, such as: exclusion or frequent dropout from child-adult contracts of adolescents in families of low socioeconomic status; or worsening of perceived mental or general health among participants receiving the Tobacco-free Duo intervention compared to those only receiving the educational component?

^a^The term *any tobacco product* encompasses the use of Swedish smokeless tobacco snus and of e-cigarettes.

**Table 2 table2:** PICO questions addressed in the experimental (cluster randomized trial) and nonexperimental (observational) studies for the effectiveness evaluation of Tobacco-free Duo.

Question		PICO^a^ description	
**Experimental**			
	**Superiority of Tobacco-free Duo comprehensive intervention vs education only in preventing smoking/tobacco onset**		
		Population	Adolescents 13 years old at baseline with valid parental consent—average follow-up 38 months
		Intervention	Tobacco-free Duo 6 components
		Comparator	Educational component of Tobacco-free Duo
		Outcome 1	Never smoked (negative answer to the question: Did you ever try smoking, even a few puffs?)
		Outcome 2	Never smoked regularly (negative answer to the question: Did you ever smoke weekly for 3 or more months in a row?)
		Outcome 3	Never used any tobacco (negative answer to both questions: Did you ever try smoking, even a few puffs? Did you try smokeless tobacco?)
		Outcome 4	Never used any tobacco regularly (negative answer to both questions: Did you ever smoke weekly for 3 or more months in a row? Did you ever use snus weekly for 3 or more months in a row?)
	**Superiority of Tobacco-free Duo comprehensive intervention vs education only in determining smoking cessation among participants’ parents**		
		Population	Parents of adolescents participating in the trial who reported smoking at baseline
		Intervention	Signing an adult-child contract
		Comparator	Receiving other intervention components, no contract
		Outcome	No past 30-day smoking at follow-up

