**Objective 1**			
	Questions 1 and 3		Is the probability of having never smoked (question 1) or used any tobacco product^a^ (question 3) at the end of follow-up in the ninth grade higher for seventh-grade adolescents in schools assigned to the full program (Tobacco-free Duo components 1-6) compared to that of adolescents in schools assigned to conduct only the educational component (component 6)?
	Questions 2 and 4		Is the probability of never having progressed to regular (weekly during at least 3 consecutive months) use (question 2: smoking cigarettes; question 4: any tobacco product) by grade 9 higher for adolescents in Tobacco-free Duo schools than for those in education-only schools?

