Participating students in schools randomized to Tobacco-free Duo or education only	Paper questionnaire, with information on: Cigarette and snus use (any, current, frequency, quitting) Tobacco use among friends and family members Received education, knowledge and attitudes toward tobacco Recent and current use of alcohol Ever use of illicit drugs General health, physical activity, and sedentary time Perceptions about the contract (if appropriate)	Self-administered in the classroom	Unique study code matched to identity information	Baseline: fall term of school year 1- grade 7 Follow-up 1: end of school year, grade 7 Follow-up 2: end of school year 2, grade 8 Follow-up 3: end of school year 3. grade 9
Guardians of the participating students above	Paper questionnaire, with information on: Sociodemographics Relation with the index child and perception of risks with tobacco use Own tobacco and alcohol use	Self-administered at home	Same code as the index child above	Same time points as above
Adults in Tobacco-free Duo pairs	Paper questionnaire, with information on: Own use of cigarette and snus Perception of own role in the intervention	Self-administered at home	Same code as the index child above	Anytime a contract is signed
All students registered in Tobacco-free Duo schools, education-only schools and reference group schools in grades 7-9	Paper questionnaire, with information on: Ever, regular and recent use of cigarette and snus	Self-administered in the classroom	No identifier (anonymous survey)	Cross-sectional surveys at the end of school year 1, 2 and 3

Figure 1 displays a scheme of the participants’ enrollment and assessments time-points for the experimental part of the study.

Individual data from questionnaires will be optically scanned, and the corresponding electronic files will be stored in a password-protected section of the server at the Department of Global Public Health, Karolinska Institutet. In order to preserve strict confidentiality, this data will be stored without personal identifiers, substituted by a study code unique to each participant. Personal identifiers will be kept in a separate section of the same server, only accessible to 2 members of the study team, responsible for data linkage and follow-up procedures, respectively. Ten years after the study start the personal identifiers will be removed and all information will be kept identified only through the study code.

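### Table 1 counts e-cigarettes as a tobacco product, but the scoring rules for Outcomes 3 and 4 in Table 2 do not, so students who used only e-cigarettes are scored as never-users

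*Protocol article*

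**What the plan says.** **Definition (Table 1).** Question 3 asks about never having "used any tobacco product^a^ (question 3) at the end of follow-up in the ninth grade". The pair on regular use is split as "question 2: smoking cigarettes; question 4: any tobacco product". Footnote a, attached to the term in Question 3, states that it "encompasses the use of Swedish smokeless tobacco snus and of e-cigarettes".

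**Scoring (Table 2, experimental part).** Outcome 3 is "Never used any tobacco (negative answer to both questions: Did you ever try smoking, even a few puffs? Did you try smokeless tobacco". Outcome 4 is "Never used any tobacco regularly (negative answer to both questions: Did you ever smoke weekly for 3 or more months in a row", with the second item "Did you ever use snus weekly for 3 or more months in a row". Each rule is complete in itself: two negative answers make a success.

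**Instruments (Table 3).** For trial students the own-use domain reads "Cigarette and snus use (any, current, frequency, quitting". For the anonymous school survey it reads "Ever, regular and recent use of cigarette and snus".

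E-cigarettes are named only once in the article, in footnote a. No other section reconciles the definition with the scoring.

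**The concern.** Two of the four adolescent outcomes in the randomised comparison carry a label that their scoring cannot support. The article does not leave the detail open. It fixes both outcomes down to the item wording, and that wording leaves out a product that its own definition includes. An analysis plan that followed Table 2 faithfully would carry the mismatch forward.

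At stake is what the trial may claim about tobacco use beyond cigarettes. The Introduction describes the programme as directed at every form of tobacco use, and objective 1 covers tobacco other than cigarettes. A report that used the Table 1 term with the Table 2 scoring would state never-use of a group of products, one of which was not counted.

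**Working it through.** **1. Definition and scoring side by side**

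| Student's history by grade 9 | Status under footnote a | Status as scored in Table 2 |
|---|---|---|
| No product of any kind | never used | never used |
| Smoked or tried smokeless tobacco, with or without e-cigarettes | used | used |
| E-cigarettes only | used | **never used** (Outcome 3) |
| Regular smoking or regular snus, with or without e-cigarettes | regular use | regular use |
| Regular e-cigarette use, neither smoking nor snus regularly | regular use | **never regular** (Outcome 4) |

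Only the third and fifth rows disagree. Students who also smoked or used smokeless tobacco (for Outcome 4, who did so regularly) are already scored as users.

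**2. Effect on the level of never-use**

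Let *s* be the recorded proportion of never-users and *f* the fraction of them who had used only e-cigarettes. Never-use under footnote a is *s*(1 − *f*), and the overstatement is *s* × *f*.

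The article gives neither quantity for Outcome 3. As an assumption, take *s* = 0.70, borrowed from the control-group figure for never smoking in the sample-size section, and let *f* vary:

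| *f* (assumed) | Never-use under footnote a | Overstatement |
|---|---|---|
| 2% | 0.70 × 0.98 = 68.6% | 1.4 points |
| 5% | 0.70 × 0.95 = 66.5% | 3.5 points |
| 10% | 0.70 × 0.90 = 63.0% | 7.0 points |
| 15% | 0.70 × 0.85 = 59.5% | 10.5 points |

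**3. Effect on the comparison between arms**

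Let *e*_T and *e*_C be the shares of all students in each arm who used only e-cigarettes. Then

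recorded difference − difference under footnote a = *e*_T − *e*_C.

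- If the shares are equal, the risk difference is unbiased.
- If *e*_T > *e*_C, the recorded effect is too favourable to the full programme.
- If *e*_T < *e*_C, for instance because the programme also reduces vaping, the recorded effect is too small.

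The risk ratio moves slightly even when the absolute shares are equal. With illustrative recorded values of 0.77 and 0.70 (ratio 1.10), removing 3.5 points from each arm gives 0.735/0.665 = 1.105, and removing 7.0 points gives 0.70/0.63 = 1.111. If instead *f* is the same in both arms, the ratio stays at 1.10. The difference then goes from 7.0 to 6.65 points at *f* = 5%. Under either form of equality, the distortion falls mainly on the level and the label.

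**4. What is not touched**

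Outcome 1 is scored from the smoking item alone and makes no claim about other products. The sample size of 3000 rests on never smoking in grade 9. The anonymous survey serves Question 7, whose outcome is never smoking, so it does not feed Outcomes 3 or 4.

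**The case against.** **Table 3 is a summary.** Its column is headed as giving main domains, and the forms are not shown. A reader might infer that the questionnaires ask nothing about e-cigarettes. The article supports only that no such item is listed. This objection stands, but it does not rescue the scoring: an item that exists on the form is still not used by the Table 2 rules.

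**Few students may be affected.** Only those who used e-cigarettes without the other products are misclassified, so it would be wrong to say that e-cigarette users in general are counted as never-users. This too stands. Some students might also answer yes to the smoking item because they have vaped. The wording does not provide for that, so relying on it would make the scoring inconsistent rather than correct.

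**The tempting stronger reading is that the scoring creates a preventive effect.** A reader might picture the programme moving adolescents from cigarettes to vaping and set a few points of such a shift against the planned 7-point difference (0.70 × 1.10 = 0.77). The documents do not support this. The 7 points belong to Outcome 1, and no target is stated for Outcomes 3 and 4. Nothing in the article suggests substitution, and the opposite bias is equally possible.

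**Nor is the powered outcome affected.** The Abstract words the primary outcome loosely, as tobacco not having been tried, which might suggest that the primary analysis is at risk. The sample-size section names never smoking as primary, and that outcome needs no e-cigarette item. The Abstract's wording is a separate matter.

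**Conclusion.** The contradiction is real and can be read directly from Tables 1 and 2. Applied as written, Outcome 3 scores students who used only e-cigarettes as never having used tobacco. Outcome 4 does the same for regular e-cigarette users who neither smoked nor used snus regularly. Both results conflict with footnote a.

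Never-use is overstated by the share of such students. The 1.4 to 10.5 points shown are illustrations that rest on an assumed 70% recorded never-use and an assumed 2% to 15% of those students having used only e-cigarettes; the article anchors neither figure for these outcomes. The comparison between arms is biased, with unknown sign, only if that share differs by arm, apart from the small shift in the ratio or the difference noted above. The case for correction rests on the mismatch between label and scoring, not on a demonstrated false effect.

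**What to change.** Make the definition and the scoring agree before the outcome analysis, in one of two ways.

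1. **Bring the scoring up to the definition.** If the student cohort questionnaire already holds e-cigarette items, or if they can be added at follow-up 3 (planned for spring 2021), require a negative answer on ever use in Outcome 3, and on weekly use for 3 or more months in Outcome 4. State which waves asked these items. The cost is at most two items and a corrected Table 2. The drawback is that baseline e-cigarette status may be unknown, so use that began before the programme could not be separated from onset, which is what objective 1 asks about.

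2. **Bring the label down to the scoring.** If no items exist and none can be added, remove e-cigarettes from footnote a and report Outcomes 3 and 4 as cigarettes or snus/smokeless tobacco. This costs only wording, but the trial then makes no statement about e-cigarettes.

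The anonymous survey needs no change for these outcomes.

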**Nonexperimental**			
	**Effect of adhering to the core component *child-adult contract***		
		Population 1	Adolescents participating the longitudinal assessment of the cluster randomized trial
		Intervention	Signing an adult-child contract (as treated)
		Comparator	Receiving other intervention components, no contract (as treated)
		Outcome	Never smoked or used tobacco at follow-up in ninth grade
		Population 2	Parents of adolescents participating the longitudinal assessment of the cluster randomized trial, baseline smokers
		Intervention	Signing an adult-child contract
		Comparator	Receiving other intervention components, no contract
		Outcome	No past 30-day smoking at follow-up

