## Abstract

**Background:**

Universal tobacco-prevention programs targeting youths usually involve significant adults, who are assumed to be important social influences. Commitment not to use tobacco, or to quit use, as a formal contract between an adolescent and a significant adult is a preventive model that has not been widely practiced or explored and has been formally evaluated even less. In this paper, we present the rationale and protocol for the evaluation of the Swedish Tobacco-free Duo program, a multicomponent school-based program the core of which rests on a formal agreement between an adolescent and an adult. The adolescent’s commitment mainly concerns avoiding the onset of any tobacco use while the adult commits to support the adolescent in staying tobacco free, being a role model by not using tobacco themselves.

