#### Components

In brief, the program aims to mobilize antitobacco practices and attitudes in adolescents’ near environments, with schools as main promoters and arenas for the activities. The recommended starting point is in the sixth or seventh grade of compulsory school (between 12 and 13 years of age), and it encompasses 6 central components that were manualized in this study.

The tobacco-free pair (Duo) core component that is the origin of the program’s name consists of an agreement between an adolescent and a significant adult (at least 18 years old) elected as partner by the adolescents. The pair agrees to remain tobacco free during the following 3 years, at least, until the index adolescent leaves the compulsory school (about 15 years of age). The written agreement is signed by both partners, possibly during a public event in school, strengthening the mutual commitment. However, a pair can be formed anytime during the school year.Student information is given by a member of the school staff who informs the student in the sixth or seventh grade about the school choice to adopt the program, briefly discusses tobacco control issues, and actively encourages participation of the adolescents.Parent information is given during an ordinary parent meeting at school where they are given access to information and materials explaining their role in tobacco prevention and how they can actively support their children in their commitment.As an incentive to participate, all adolescents signing a contract will receive a membership card that entitles them to some fringe benefits in local shops or leisure-time activities.At the end of each school year, the pairs disclose and confirm their tobacco-free status. The disclosure entitles the index adolescent to participate in a lottery taking place just before the summer break.Interactive classroom education is conducted by trained school personnel in all classes during grades 6 (or 7) to 9. This education consists of age-specific information and practical exercises (eg, how to identify and resist social influences). For the purpose of this evaluation, the educational part was further structured and manualized before training personnel.

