**Objective 2**			
	Question 5		Is the probability of having refrained from using cigarettes or any tobacco by the end of follow-up higher among adolescents and parents who smoke who signed the formal agreement to become a tobacco-free pair (core component) compared to those who only received other components?
	Question 6		Is the proportion of sustained quitters (no smoking in the past 30 days) among parents who smoke before the program’s start higher when the index child attended a Tobacco-free Duo school compared to an education-only school, at the end of the compulsory grades?

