### Data Collection and Management

At both baseline and follow-up, information on outcome and predictor variables will be collected at 2 levels.

School-level information will encompass compositional and organization measures such as number of registered students and staff, staff average qualification, proportion of students with parents with lower than high school education, proportion of students with parents born outside Sweden, public or private management, and prior and current health promotion initiatives or preventive programs. Structured checklists and questionnaire forms will be developed.

In schools participating in the experimental part of the study, information will be continuously collected about the actual implementation of the intervention components and staff effort dedicated to them. To this end, a structured web-based form will be used.

Individual-level information will be gathered from individual students in Tobacco-free Duo schools, education-only schools, and reference group schools; from parents of students in Tobacco-free Duo and education-only schools; and adults in Tobacco-free Duo schools signing the contract with individual students, when not coinciding with one parent. All information will be collected with self-completed structured questionnaires with different content and administered with different procedures as shown in Table 3. All questionnaires will be based on sets of questions that have been previously used in Swedish surveys or longitudinal studies of tobacco use in youths. Individual participants in the experimental study will be traced through school records, even in cases of change of school or residence address. In fact, during compulsory education, changes of schools are registered at both ends of the transition (former and new school). Those absent during data collection days will be reached at their latest registered residence addresses.

**Table 3 table3:** Data collection instruments, information, and procedures.

Population	Instrument and main domains	Administration	Identifier	Time-points

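### The parental contract comparison classes baseline smokers by whether they ever sign, so a quit that came before signing can be counted as a success of the contract

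*Protocol article*

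**What the plan says.** Table 2, under the nonexperimental effect of the core component, defines Population 2 as "Parents of adolescents participating the longitudinal assessment of the cluster randomized trial, baseline smokers". Exposure is signing an adult-child contract, the comparator is receiving other components without a contract, and the outcome is no smoking in the 30 days before follow-up. The parental row under the Experimental heading of Table 2 uses the same exposure and comparator wording. Question 5 in Table 1 asks the matching question about "adolescents and parents who smoke who signed the formal agreement to become a tobacco-free pair".

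On what is promised, the Components section states: "The pair agrees to remain tobacco free during the following 3 years, at least". It adds that a pair may form at any point in the school year. The abstract describes the general model as "Commitment not to use tobacco, or to quit use, as a formal contract between an adolescent and a significant adult", and this program's adult as "being a role model by not using tobacco themselves". The Discussion, on side effects, describes a breach by the adult only as taking up smoking or going back to it.

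Table 3 has adults in Duo pairs report their own cigarette and snus use, at the time point "Anytime a contract is signed". It also has guardians report their own tobacco use at baseline and at the end of grades 7, 8 and 9.

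**The concern.** A parent who smokes at baseline cannot, on the literal Components wording, promise to remain tobacco free until he or she has stopped. Such a parent would move into the signing group because of a quit, and that quit, if it lasts, is then scored as the outcome. Exposure would partly be a consequence of the outcome.

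The Data Analysis section and the Discussion warn that the as-treated comparison is open to confounding and point to adjustment. Adjusting for characteristics measured at baseline does not repair an exposure that is set after the quit. A favorable result could then be read as evidence that the contract helps parents stop smoking, when it shows only that parents who have stopped are readier to sign.

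**Working it through.** **Stated figures.** The article gives no sample size, quit rate or signing rate for this comparison, so there is nothing to reproduce. Every rate below is an assumption.

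**Inputs, with the contract assumed to have no effect.**
- q: share of baseline-smoking parents abstinent at grade 9; 0.10 to 0.20.
- e: share of those quitters who had already quit before they could sign; 0, 0.25 or 0.50.
- s1: signing rate among parents who have already quit; 0.60.
- s0: signing rate among parents still smoking; 0.30, 0.10 or 0.

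**Formulas.**
- P(sign | quitter) = e·s1 + (1 − e)·s0
- P(sign | continuing smoker) = s0
- Bayes' rule then gives abstinence among signers and among non-signers, and their ratio is the apparent risk ratio.

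**Worked case, q = 0.15, e = 0.25, s0 = 0.30.**
- P(sign | quitter) = 0.25 × 0.60 + 0.75 × 0.30 = 0.375.
- Signers: 0.15 × 0.375 / (0.15 × 0.375 + 0.85 × 0.30) = 0.05625 / 0.31125 = 18.1%.
- Non-signers: 0.15 × 0.625 / (0.15 × 0.625 + 0.85 × 0.70) = 0.09375 / 0.68875 = 13.6%.
- Risk ratio 1.33, although the true value is 1.

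**Apparent risk ratio with no contract effect (range over q = 0.10 to 0.20).**

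| Signing rate among parents still smoking | e = 0 | e = 0.25 | e = 0.50 |
|---|---|---|---|
| 0.30 | 1.00 | 1.30–1.35 | 1.66–1.78 |
| 0.10 | 1.00 | 2.03–2.29 | 3.05–3.77 |
| 0 (only tobacco-free adults sign) | no signers | 5.7–11.6 | 6.7–13.9 |

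In the last row every signer has quit by definition.

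**Why timing has to be in the formula.** A simpler model gives eventual quitters a signing rate a and continuing smokers a rate b, with no timing. At q = 0.15, a = 0.5 and b = 0.1, abstinence is 0.075 / 0.160 = 47% in signers and 0.075 / 0.840 = 9% in non-signers. The same figures would arise if motivated parents signed while smoking and quit later, which is ordinary confounding. Only b = 0 is specific to reverse order in that model, so I do not rely on it.

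**Effect of a common landmark.** Suppose the early quits and the signing both fall before the landmark, and keep only parents still smoking then. Early quitters leave both groups, and later quitters and continuing smokers sign at the same rate s0. Abstinence is q(1 − e) / (1 − qe) in signers and non-signers alike. At q = 0.15 and e = 0.25 that is 0.1125 / 0.9625 = 11.7% in each, a risk ratio of 1.0. This needs s0 above zero. If no smoker can sign, no parent signs while smoking and the effect on quitting cannot be estimated.

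**The case against.** Several points on the other side carry weight.

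- **A reader might infer a flat contradiction over what the adult promises.** The documents do not support that. The abstract's mention of quitting describes the contract model in general, and Question 5 speaks of parents who smoke and signed. A smoker could pledge to be tobacco free for the coming three years. What stands is an unresolved ambiguity.
- **A reader might infer that the comparison is bound to show a large benefit.** It is not. The risk ratio is 1.00 if nobody quits before signing. The pledge runs to the end of grade 9, so much of the signing may fall close to the grade 7 baseline, leaving little time to quit first. Open-ended signing still leaves the route available.
- **A reader might infer that status at signing is not collected from parents**, because Data Collection and Management lists "adults in Tobacco-free Duo schools signing the contract with individual students, when not coinciding with one parent". Parents are already named in that list, so the clause more plausibly avoids naming them twice, and Table 3 gives the form to all Duo adults. That sentence needs no correction.
- **Signing windows and landmarks are often left to an analysis plan**, which is not shown. That is fair as to detail. But Table 2 itself fixes population, exposure, comparator and outcome, and as fixed they allow a quit to precede exposure.
- **The analysis is secondary and openly described as prone to bias.** True, and it limits the grade. The stated caveat concerns confounding, which is a different problem. Question 6 asks about parental cessation by assigned school and, as worded in Table 1, is not affected.

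**Conclusion.** The point holds in a limited form. As Table 2 defines the parental comparison, baseline smokers are classed by whether they ever sign, whatever their tobacco use at that moment, so a quit can both lead to signing and count as the outcome. The direction is toward an apparent benefit of the contract.

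The size cannot be derived from the documents. With no true effect, s1 = 0.60 and q = 0.10 to 0.20, the apparent risk ratio is about 1.3 to 3.8 when 25% to 50% of quitters quit before signing and 10% to 30% of parents still smoking sign. It is 1.0 when none quit first, and 5.7 to 13.9 when only parents already tobacco free can sign.

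The randomized adolescent comparison and the primary outcome are untouched. I would class this as a cheap improvement to a stated secondary question.

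**What to change.** 1. In Table 2, Population 2, define exposure as the parent personally having signed by one common landmark, for example the end-of-grade-7 survey. Restrict signers and non-signers alike to parents still smoking at that landmark, and compare abstinence at grade 9. The restriction must be the same in both groups. Asking signers only to be smoking when they signed would keep their quits between signing and landmark while excluding the same quits among non-signers, which favors signing.
2. Use the form completed at signing and the guardian questionnaires to identify parents already abstinent when they signed. Report them separately, not as exposed successes.
3. State that a parent whose child signed with another adult is not a signer.
4. Carry the same definition to the parental row under the Experimental heading wherever signing is used as exposure there.
5. Reconcile the abstract, the Components section and Question 5 on what a smoking adult promises. Which rule applies is for the investigators. If no current smoker may sign, the comparison cannot estimate an effect on quitting, and the plan should say so.

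The cost is wording and a restricted secondary analysis on data that Table 3 already plans to collect. There will be fewer exposed parents, and quits between signing and the landmark drop out, so the estimate is less precise and conservative. Ordinary confounding remains and still needs the planned adjustment.
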